#### Questionnaires

Self-report information in the form of a questionnaire will be administered by staff at baseline (pregnancy) and when children are aged 24- and 36-months. The questionnaire was pilot-tested using focus groups comprised of members of participating Indigenous communities and Aboriginal Maternal Infant Care workers, with the questions revisited and refined during Year 1 of the research. Questionnaire items were modelled on those used in both Australian [26] and international population-level surveys [27,28] and include carers’ self-reported ECC experience of their child, as well as carers’ oral health knowledge, oral self-care, dental service utilisation, oral health-related self-efficacy and oral health literacy.

Covariates include socio-demography, oral health and general health. Socio-demographic covariates (collected at baseline only) include age, Indigenous affiliation, residential location, education level, employment, gross household income, house ownership, number of children, number of people who stayed in house the previous night, and car ownership. Oral health covariates include carer self-reported oral health, oral health-related quality of life, and history and experience of dental services of both the parent and child. General health covariates include parent behaviours such as tobacco smoking, alcohol consumption and self-reported general health.

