### Statistical Analysis

Test-immediate and control-delayed intervention groups will be compared at baseline, 24- and 36- months. Results will be compared using the Generalized Linear Mixed Model (GLMM) approach to focus on variation in the primary outcome: early childhood caries levels. All participants who completed the 24-month follow-up ECC-related outcome data will be included in multivariate modelling. Analysis will include fitting GLMM models for analysis of the correlated data in order to determine factors associated with ECC-related changes. Missing data will be addressed by the GLMM estimating mechanism, which assumes interdependence between repeated measures of participants, copes well with random missing data, allows for different intercepts and rates of change, and provides good predictive models. All variables showing associations at p < 0.15 in the GLMM univariate analyses will be entered into multivariate models using a stepwise approach. All effects will be estimated with 95% confidence intervals, with statistical significance taken as a two-sided p-value less than 0.05. This data will contribute to the inter-country analysis.

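### The GLMM is named as the remedy for missing data, but it does not cover missing covariates, so the multivariable model includes every child with 24-month ECC data only if all selected covariates are complete

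*Protocol article*

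**What the plan says.** Three statements in the protocol article's Statistical Analysis section bear on this point.

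- Missing data: "Missing data will be addressed by the GLMM estimating mechanism". The same sentence says that this mechanism "copes well with random missing data". It does not separate outcomes from covariates, and no other method is named anywhere in the article.
- Analysis set: "All participants who completed the 24-month follow-up ECC-related outcome data will be included in multivariate modelling".
- Covariates: "All variables showing associations at p < 0.15 in the GLMM univariate analyses will be entered into multivariate models using a stepwise approach".

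The candidates are listed under Questionnaires. The socio-demographic group begins: "Socio-demographic covariates (collected at baseline only) include age, Indigenous affiliation, residential location, education level, employment, gross household income". It continues with house ownership, number of children, household occupancy and car ownership, which makes ten items. The other two groups are introduced with "Oral health covariates include carer self-reported oral health, oral health-related quality of life" (plus dental service history and experience) and "General health covariates include parent behaviours such as tobacco smoking, alcohol consumption and self-reported general health", about three items each. That is roughly 16 candidates, nearly all reported by the carer.

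**The concern.** The concern is about children whose ECC outcome was observed but for whom a covariate value is missing. It is not about children who missed an examination. For the latter, a likelihood-based GLMM is a reasonable choice under missing at random. For the former, it offers nothing: the likelihood is written conditional on the predictors, so a record with a blank predictor cannot contribute to it.

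An analyst who follows the section as written would therefore exclude children whom the same section says are included. Income, alcohol and tobacco items are the kind that carers may decline to answer. If follow-up versions of the oral and general health items are used, a child who was examined but whose carer did not complete that questionnaire is also lost. Because variables enter stepwise, the set of children with complete data can differ between steps, so p-values at successive steps may come from different children. What is at stake is some power, and a clear statement of whom the adjusted estimates describe.

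**Working it through.** **1. The plan's own figure.** Sample size section: 250 evaluable children, 35% attrition. 250 / (1 - 0.35) = 384.6, so 385. This matches the article, which then rounds up to 400. Children expected with outcomes: 400 x 0.65 = 260, or 130 per arm.

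**2. Margin before the count falls below 250.** (260 - 250) / 260 = 3.8%. Losing more than about 4% of outcome-observed children leaves fewer than 250.

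**3. How a mixed model treats a blank covariate.** As an illustration, a linear mixed model was fitted to simulated data: 260 children, two visits, about 10% of outcomes removed, and one baseline covariate missing in about 15% of children. Without the covariate, all 470 observed outcome records were used. With it, 413 were used. All 57 dropped records had an observed outcome.

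**4. Power after loss.** The article gives neither the control prevalence nor whether 25 percent is relative or absolute, so both readings are shown with assumed prevalences. With n per arm, d = p1 - p2 and p̄ = (p1 + p2)/2, two-sided 0.05:

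power = Φ{ [d - 1.96 √(2p̄(1-p̄)/n)] / √([p1(1-p1) + p2(1-p2)]/n) }

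| Share with a blank selected covariate (assumed) | Children left | Relative: 0.70 vs 0.525 | Absolute: 0.625 vs 0.375 |
|---|---|---|---|
| 0% | 260 | 0.83 | 0.98 |
| 10% | 234 | 0.79 | 0.97 |
| 20% | 208 | 0.74 | 0.96 |
| 30% | 182 | 0.68 | 0.93 |

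The relative assumption is close to the stated design: a 25% relative reduction needs 125 per arm at a control prevalence of about 0.69. An absolute 25-point difference needs at most 62 per arm (70 with continuity correction).

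**5. What item-level rates could produce such losses.** If items are missing independently at rate m, the number left with k covariates is 260 x (1 - m)^k. At m = 2%: k = 10 leaves 260 x 0.817 = 212, and k = 16 leaves 260 x 0.724 = 188. If instead the blanks all fall in the same carers, 5% per item leaves 260 x 0.95 = 247 whatever k is.

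**6. The starting number.** The 35% attrition applies at 36 months, whereas the analysis set is defined at 24 months. With a constant dropout rate (assumed), 24-month retention is 0.65^(24/36) = 0.75, or about 300 children. The loss would then have to exceed (300 - 250) / 300 = 17% before the count fell below 250.

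**The case against.** **This is detail for the analysis plan.** Covariate item non-response is often left to a statistical analysis plan, which is not shown here. The missing-data sentence also speaks of repeated measures, intercepts and rates of change, which is language about outcomes; on that reading it is correct and covariates are simply not mentioned. This has weight. But the article is not silent: it names one mechanism for missing data without qualification and fixes an inclusion rule that this mechanism cannot secure. An analysis plan written faithfully to it would carry the gap forward.

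**A reader might infer that the two statements flatly contradict each other.** They do not. Both hold if every selected covariate is complete. Staff administer the questionnaire and carers receive a fifty-dollar gift card for each one, so completeness may be high. The article gives no evidence either way.

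**A reader might infer that the trial's arm comparison rests on complete cases.** The article does not say that the stepwise model supplies the arm effect. It also plans group comparisons at each time point and univariate GLMMs, and a GLMM with arm alone loses no child to a blank covariate. The stepwise model may serve mainly the stated aim of finding factors associated with ECC changes.

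**A reader might infer that 250 will not be reached, or that power falls to the 60s.** Neither follows from the documents. The first needs a loss above about 4% from 260, or about 17% from 300. The second needs a loss of nearly 30% and the relative reading. Independent missingness, all 16 covariates surviving selection and the 36-month retention figure each push the result in the pessimistic direction.

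That carers who skip items differ from those who do not is plausible, but the documents cannot show it.

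**Conclusion.** The point stands in conditional form. The missing-data method named in the Statistical Analysis section covers missing ECC outcomes and does not cover missing covariates. If any selected covariate is incomplete, children promised a place in the multivariable model will be dropped, and the analysed set can shift between stepwise steps.

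The size cannot be fixed from the article. A 10% loss costs about 4 points of power under the relative reading and about 1 under the absolute reading; a 30% loss costs about 15 and about 6. These figures rest on assumed prevalences, on 260 children with outcomes and on an assumed share with a blank covariate. They are smaller if blanks cluster in the same carers or if 24-month retention exceeds 65%. Any loss of representativeness is a reasonable worry but is not quantified. The flaw is modest and cheap to repair, and is best settled before the data are analysed.

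**What to change.** In the Statistical Analysis section:

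- Limit the GLMM sentence to missing ECC outcomes.
- For the randomised arm effect, adjust only for baseline covariates. Fill missing baseline values without using arm or outcome (the mean for a continuous item, a missing category for a categorical one), so that every child with an ECC outcome is retained.
- For the models of factors associated with ECC, and for any covariate measured at follow-up, use multiple imputation. Simple filling can distort the associations those models are meant to estimate.
- Keep one fixed analysis set across all model-building steps, and report the number analysed in each model.

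The cost is a few sentences and a little more analysis work. The drawback is that, where simple filling is used, the filled covariates' own coefficients should not be interpreted.

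### The p<0.15 screen with stepwise entry leaves the arm effect open to adjustment for a variable on the treatment pathway, and no primary arm model is set apart from it

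*Protocol article*

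**What the plan says.** The Statistical Analysis section describes one modelling approach with two aims. The first is the comparison of the arms: "Results will be compared using the Generalized Linear Mixed Model (GLMM) approach to focus on variation in the primary outcome: early childhood caries levels". The second is a search for explanatory factors: the models are fitted "in order to determine factors associated with ECC-related changes". One selection rule follows: "All variables showing associations at p < 0.15 in the GLMM univariate analyses will be entered into multivariate models using a stepwise approach". The section then promises 95% confidence intervals for all effects and a two-sided 0.05 criterion.

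The candidates are set out under Questionnaires: "Covariates include socio-demography, oral health and general health". A timing limit is attached to the first domain alone: "Socio-demographic covariates (collected at baseline only) include age, Indigenous affiliation, residential location", and so on. The oral health and general health domains carry no such limit, and the questionnaire is "administered by staff at baseline (pregnancy) and when children are aged 24- and 36-months". One oral health covariate is "history and experience of dental services of both the parent and child".

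**The concern.** Randomisation makes a comparison of the arms interpretable without searching for confounders. A screen on association with the outcome, followed by stepwise entry, is a tool for finding risk factors. Applied to the arm comparison, it raises two problems.

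- **Adjustment on the pathway.** A variable that the intervention changes, and that in turn affects caries, tends to pass a screen on association with caries. Once it is in the model, the arm coefficient measures only the part of the effect that bypasses it. Child dental attendance may also be a consequence of caries, which would add a bias of less predictable direction.
- **Inference after selection.** Nominal intervals and p-values treat the final model as if it had been fixed in advance.

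At stake is the primary contrast of the trial: a real benefit could be reported as smaller than it is, or as non-significant.

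**Working it through.** **Step 1. Can a candidate covariate be post-randomisation and affected by the intervention?** Set the sections side by side.

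- Participants and recruitment: at enrolment the child is unborn or under six weeks old.
- Questionnaires: dental-service experience of parent and child is a covariate, with no baseline limit. For the child, a baseline value has no content, so usable values come from 24 or 36 months.
- Intervention review: dental care is arranged for immediate-arm participants in pregnancy or up to six weeks after birth, and their 18-month motivational session encourages enrolling the child for a dental check.

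For the child's part of the item the answer is yes. For smoking, alcohol, carer oral health and the parent's dental history, a baseline value exists and could be the one used.

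**Step 2. The plan's own figure.** Evaluable 250, attrition 35%: 250/(1 - 0.35) = 384.6, so 385, which agrees with the Sample size section. The 400 planned leave 400 × 0.65 = 260 children, used below. The point does not depend on this figure.

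**Step 3. Size.** The documents give no mediation inputs, so everything here is assumed: a single-visit logistic model, 260 children, covariate M = 0.8 × arm + standard normal noise, and a total log odds ratio of about -0.71 (odds ratio about 0.5), of which a share s runs through M. The adjusted arm log odds ratio is then about -(1 - s) × 0.71. For s = 0.5 this is -0.355, and exp(-0.355) = 0.70. Unadjusted power was about 0.74-0.80.

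| Share through M | Adjusted odds ratio | Power of adjusted arm test |
|---|---|---|
| 10% | 0.53 | 0.63 |
| 25% | 0.58 | 0.51 |
| 50% | 0.70 | 0.25 |
| 75% | 0.83 | 0.10 |

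**Step 4. Cross-check with a different set-up.** Assumed control prevalence 0.69 and a relative 25% reduction (0.69 × 0.75 = 0.5175), 125 per arm, and a binary covariate present in 35% of control and 65% of immediate carers. Unadjusted power was 0.78-0.81 and the unadjusted odds ratio about 0.48.

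| Share | Adjusted odds ratio | Power of adjusted arm test | Arm kept after screen and backward elimination |
|---|---|---|---|
| 0% | 0.48 | 0.74 | 0.77 |
| 25% | 0.57 | 0.51 | 0.55 |
| 50% | 0.68 | 0.27 | 0.27 |
| 75% | 0.81 | 0.12 | 0.12 |

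Backward elimination at 0.05 is one assumed form of the stepwise rule, with arm treated as a candidate. The two set-ups agree on direction and closely on size.

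**The case against.** **The rule may serve only the factor search.** The section opens with a plain commitment to compare the groups at baseline, 24 and 36 months, and the factor search has its own stated aim. A reader might infer that arm must itself pass p<0.15. The text does not say so; it only fails to exempt arm. That stands, but no separate arm model is described either, so the ambiguity remains.

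**Follow-up covariate values are never said to enter the model.** This also stands. The inference is strong only for the child's dental-service item. A reader might conclude that all oral and general health covariates are post-randomisation; the documents do not support that.

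**The randomised effect is not necessarily lost.** If arm is among the variables analysed one at a time, the univariate step gives an estimate unadjusted for covariates. It would therefore be too strong to say that the reported effect will no longer be the randomised one. The defect is that the plan does not say which estimate is primary.

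**Much of the effect may bypass dental attendance.** Study staff apply the varnish, often at home, and the 6-month session addresses diet. A small share is plausible, which is why a range is given.

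**Two tempting figures show little harm.** At 80% power, arm would fail the p<0.15 screen with probability P(Z > 1.960 + 0.842 - 1.440) = P(Z > 1.362) = 0.087; at 50% power, P(Z > 0.52) = 0.30. Those trials already have p>0.05, so no significant result is lost. Of the 16 named covariates, 16 × 0.15 = 2.4 would pass on average if all were noise, and at least one with probability 1 - 0.85^16 = 0.93 if they were independent. Noise covariates measured at baseline do not bias a randomised contrast, and several of the 16 are plainly correlated.

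**An article may leave detail to the full plan.** It may, but this rule is stated, not omitted.

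**Conclusion.** The point holds in conditional form. The article fixes a data-driven selection rule for the only model it describes for the primary outcome, without protecting the arm term or restricting candidates to baseline. At least one named candidate has a component that arises after randomisation and that the intervention promotes. The arm effect can therefore be adjusted for part of its own mechanism, and inference after selection is not valid at its nominal level.

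The attenuation runs from slight (odds ratio 0.53 at a 10% share) to near-complete (0.83 at 75%), with power from 0.63 down to 0.10. These values rest on the assumed share, covariate shift and effect size, and on a single-visit model in place of the repeated-measures GLMM. The move towards no effect requires that the covariate carries part of the benefit. The criticism of the nominal intervals and p-values needs no mediation assumption.

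**What to change.** Replace the selection sentence with text to this effect:

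- The primary analysis is a GLMM with study arm and visit forced in, the arm contrast estimated at 24 months (for example through an arm-by-visit term), and recruitment site included as the stratification factor.
- Further covariates are limited to a short list of baseline variables, named before the outcome data are released.
- No variable measured after randomisation enters the treatment-effect model.
- Screening at p<0.15 and stepwise selection are confined to a separately labelled exploratory risk-factor analysis.

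The arm-by-visit term is one way to obtain the 24-month contrast, not the only one. If the stepwise rule was always meant for the factor search alone, the same wording makes that explicit. The cost is a change of analysis text, with no new data and no change to the conduct of the trial.

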## Discussion

This study could provide a foundation for preventive dental care and oral health education among Indigenous children, reducing oral disease in childhood. The unique approach of combining four interventions of known efficacy in preventing or reducing early childhood caries will potentially enable greater benefits. The control-delayed intervention design satisfies many of the ethical concerns raised, in Australia at least, when conducting traditional randomised controlled trials among Indigenous populations (in which the control arm typically receive ‘standard course-of-care’ or no benefits at all) [25,29].

This study is timely, as most countries recognize the oral health of Indigenous children to be an important yet often over-looked area of both research and policy. Because each country participating in the study (i.e. Australia, New Zealand and Canada) has unique Indigenous population groups in terms of history and geographic isolation, our data will enable country, community and individual-level comparisons. The governments of Australia, New Zealand and Canada recognize Indigenous child oral health to be a priority in their respective national oral health plans; and Indigenous groups in these nations emphasise that children’s oral health is of key importance. Developing culturally-appropriate interventions which utilise Indigenous frameworks and research methodologies may provide evidence which leads to more appropriate oral health initiatives for Indigenous children, reducing global oral health inequalities.

## Abbreviations

AG, Anticipatory guidance; dmft/s, Decayed, missing or filled teeth/surfaces in the primary dentition; ECC, Early childhood caries; GLMM, Generalized linear mixed model; MI, Motivational interviewing; MS, Mutans streptococci; NHMRC, National Health and Medical Research Council of Australia.
